**Methods/design:**

Study participants are families consisting of three persons: an adult woman, her male husband or partner, and one of her children aged 8–17 (if available). Eligibility criteria include experience of moderate-to-severe intimate partner violence by the woman and hazardous alcohol use by her male partner. Family units are randomized to receive CETA or treatment as usual. The primary outcome is VAWG as measured by the Severity of Violence Against Women Scale, assessed along with secondary outcomes at 24 months post-baseline. Interim assessments are also conducted at 4–5 months (following CETA completion) and 12 months post-baseline.

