### Assessment of outcomes and follow-up

Post-assessments were conducted with participants starting in October 2016 and are ongoing. All post-assessments (4/5, 12, and 24 months post-baseline) are conducted in the same format (i.e. ACASI), and at the same locations as baseline. At baseline and all follow-up visits, participants are provided with reimbursement for travel. The primary outcome in the study is violence as measured by the SVAWS. Secondary outcomes include alcohol and other SU, mental health, psychological violence, and gender norms. Each participant type (woman, man, child) completes a specific battery of instruments via ACASI. The measures included in ACASI were pilot tested with participants sampled from the same source population as those in the trial to check translation accuracy and item comprehension. In addition to the self-report measures administered via ACASI, a hair sample is collected from participants as a biomarker of chronic stress (Russell *et al.*
2012). The full list of outcome instruments is displayed in Table 2.

**Table 2. tab02:** Primary and secondary outcome measures for VATU trial

				Cronbach's *α*^a^		
Measure	Construct	Reference	Description	Woman	Man	Child
Primary outcome						
Severity of Violence against Women Scale (SVAWS)	Violence	Marshall (1992)	46 items assessing how often (never, once, a few times, many times) a current partner perpetrated acts of violence against the participant in the past year. Subscales include: (a) threats of violence; (b) physical violence; and (c) sexual violence. Previously used in a study of IPV among women with partners who have alcohol abuse in South Africa (Peltzer & Pengpid, 2013)	0.95	–	–
Secondary outcomes						
World Health Organization IPV measure (WHO-IPV)^b^	Violence	World Health Organization (2005)	Nine items assessing how many times a current or previous partner ever and recently perpetrated acts of violence (never, once, a few, many). Previously used in the WHO multi-country study on Women's Health, including in Tanzania and Namibia	0.95	0.96	–
Youth Victimization Scale (YVS)	Violence	Nadel *et al*. (1996)	135 items assessing how often (never, once, sometimes, often) youth have experienced various types of recent violence at school, in the neighborhood, and at home	–	–	0.98

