### Data and safety monitoring

The trial is monitored by a four-person Data Safety Monitoring Board (DSMB). It was mutually determined between DSMB members and study investigators that if the CETA intervention displayed statistically significant effectiveness with at least a moderate effect size at the 12-month follow-up assessment, it would be ethically appropriate to stop the trial and offer the intervention to control participants. Therefore, the DSMB will conduct an effectiveness analysis following the completion of the 12-month post-baseline assessments. The trial will be unmasked and stopped if there is a statistically significant difference between the change in primary outcome (i.e. SVAWS score among female participants) by treatment arm, defined as a Cohen's *d* effect size of ⩾0.5 and a *p* value of <0.05. In that scenario, control participants would not be assessed at 24 months post-baseline but would be offered CETA, and CETA participants would still be assessed at 24 months as planned to measure whether treatment effects were sustained. If no significant difference in change in SVAWS score by treatment arm is found in the 12-month DSMB analysis, the trial will continue as planned with all participants assessed at the primary study endpoint of 24 months (see Fig. 1).

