### Data analysis

Sample size calculations were informed by a study conducted in South Africa that used the SVAWS physical violence subscale to measure violence among women who had been abused by a partner with an alcohol use problem (Peltzer & Pengpid, 2013). We calculated the sample size needed to obtain a 20% reduction in SVAWS physical violence subscale score among intervention participants at a 24-month follow-up, assuming no change among control participants, using a two-sample independent means *t* test. For 80% power at an *α* level of 0.05, we calculated that we would need to enroll a minimum of 50 families in each study arm to detect this difference in change in means, which we inflated to 84 per arm to account for loss to follow-up and the possibility of small clustering effects at the provider level.

All primary analyses will be based on an intent-to-treat approach with all participants who were randomized included in the final analysis. Loss to follow-up and missing data will be addressed by using multiple imputation (Azur *et al.*
2011). We will estimate linear (continuous outcomes) and generalized linear (binary outcomes) mixed-effects models that will incorporate a random intercept term to account for within-subject correlation on repeated measures. The outcome scores at the three follow-up times will be modeled separately using treatment arm, baseline symptom score (if there is a meaningful difference between the study arms at baseline), time, and an interaction between each treatment arm and time as fixed covariates in each model.

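### The primary model sentence cannot be fitted as written, its baseline adjustment has no effect under the best-supported reading, and the powered SVAWS score is not the outcome as named

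*Protocol article*

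**What the plan says.** **Model.** The Data analysis section of the protocol article specifies mixed models that "incorporate a random intercept term to account for within-subject correlation on repeated measures". It then says "The outcome scores at the three follow-up times will be modeled separately using treatment arm, baseline symptom score", where the baseline score enters only "if there is a meaningful difference between the study arms at baseline". The list of terms ends with "time, and an interaction between each treatment arm and time as fixed covariates in each model". No coefficient or contrast is named as the primary test.

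**Time point.** This is fixed. The abstract says "The primary outcome is VAWG as measured by the Severity of Violence Against Women Scale, assessed along with secondary outcomes at 24 months post-baseline", and the Data and safety monitoring section also treats 24 months as the primary endpoint.

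**Score.** The abstract and the Assessment of outcomes and follow-up section name the SVAWS without a subscale. Table 2 describes it as 46 items: "Subscales include: (a) threats of violence; (b) physical violence; and (c) sexual violence". The 12-month stopping rule is on "SVAWS score among female participants", again with no subscale. The sample size paragraph differs: "We calculated the sample size needed to obtain a 20% reduction in SVAWS physical violence subscale score among intervention participants". Eligibility and the baseline table (Table 3) also use the physical violence subscale.

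**The concern.** Modelling each follow-up separately means one outcome row per woman per model. A time effect, an arm-by-time effect and a within-woman random intercept all need at least two rows per woman. The sentence therefore conflicts with itself, and an analyst has to choose a reading. The readings that can be fitted do not all put the treatment effect in the same coefficient.

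The baseline score raises a second problem. It is to be added when the arms look different at baseline, by a criterion that is not defined. Whether adding it changes anything depends on which model is fitted.

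The score raises a third. Elsewhere the article names the physical subscale when it means it, so the unqualified name reads naturally as the full scale. If so, the power statement concerns a different score from the primary outcome. The stopping rule (d of at least 0.5 and p below 0.05) inherits the doubt, and that rule decides whether controls are assessed at 24 months at all.

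**Working it through.** **1. Can the sentence be fitted as written?** Take one follow-up, say 24 months, with columns intercept, arm, time, arm × time. Time is 24 in every row, so time = 24 × intercept and arm × time = 24 × arm. There are four columns but the rank is 2: time and arm-by-time are not estimable, and a random intercept has no repeats to work on. Baseline plus one follow-up gives rank 4 of 4. All three follow-ups with categorical time give rank 6 of 6. Both of these can be fitted.

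**2. Which reading does the article favour?** The sample size paragraph and the stopping rule both speak of a between-arm difference in change. Baseline plus one follow-up per model fits that, and also fits separate models and repeated measures.

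**3. What does the baseline covariate do there?** Write y(i,t) = α + β·arm + γ·t + δ·arm·t + λ·b(i) + u(i) + e(i,t), with t = 0 or 1 and b(i) the baseline score. Subtracting the two rows gives

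y(i,1) − y(i,0) = γ + δ·arm + error.

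Both λ·b(i) and u(i) cancel. With both rows present (or imputed), the estimate of δ is the difference in mean change, with or without b. In a simulated data set with a 0.25 SD baseline imbalance, arm-by-time was −0.490 with the covariate and −0.490 without it; analysis of covariance on the follow-up score gave −0.378. The statement concerns the estimate. The printed standard error can move, because baseline is then both an outcome row and a covariate, but that is not adjustment.

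**4. The plan's own sample size.** The planning mean and SD are not given, so 50 per arm can only be inverted. At 80% power and two-sided 0.05 (sidedness assumed), d = (1.96 + 0.842) × √(2/50) = 0.560, or 0.566 with the t distribution. For comparison, 20% of the trial's baseline mean of 60.7 is 12.14 points; with SD 16.8, d = 0.72, needing about 31 per arm. The figure of 50 is neither confirmed nor refuted.

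**5. Power by reading.** Inputs: 248/2 = 124 per arm; 30% loss (the upper figure in the section on modifications) gives 124 × 0.70 = 86.8, taken as 87; d = 0.566; ρ, the correlation between baseline and 24 months, is assumed. Clustering by provider is ignored.

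- Difference in change: standardised effect d/√(2(1 − ρ))
- Baseline-adjusted contrast: standardised effect d/√(1 − ρ²)
- Power ≈ Φ(effect × √(87/2) − 1.96); the values below use the t distribution.

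| ρ | Change: effect, power | Adjusted: effect, power |
|---|---|---|
| 0.2 | 0.447, 83.5% | 0.578, 97% |
| 0.3 | 0.478, 88% | 0.593, 97% |
| 0.5 | 0.566, 96% | 0.653, 99% |

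The change test has 80% power at an effect of 0.427, so it falls below 80% only if 2(1 − ρ) exceeds (0.566/0.427)² = 1.757, that is, if ρ is below about 0.12.

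**6. The score.** The article gives no mean, SD or expected effect for the full 46-item score, so its power cannot be computed.

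**The case against.** The strongest reply is that the article does point to one workable model. Its repeated references to change select baseline plus one follow-up, whose arm-by-time term is exactly that quantity. The baseline covariate is then merely redundant. Change scores and analysis of covariance are both valid under randomisation, and a separate analysis plan may name the coefficient. Much of this stands, and it is why the point is not that no analysis can be run. It does not remove the defect: a plan would have to override the printed sentence rather than elaborate it, and a stated adjustment that adjusts nothing is an error in the text.

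On the score, the reply is that the words total score never appear, that screening on a subscale while analysing the wider scale is no contradiction, and that planning from the score used in the source study is ordinary. That also stands. What is shown is an unnamed primary score, not proof that the tested and powered scores differ.

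Two stronger inferences are tempting, and the article supports neither.

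- A reader might infer that the primary test is underpowered. Power well below 80% appears only if d is back-solved to 0.427, the value giving exactly 80% at 87 per arm. That d is not the article's; its own 50 per arm implies 0.566.
- A reader might infer that the test would miss a constant, lasting benefit. That needs all follow-ups in one model and the interaction alone as the primary test. The article says neither, and from such a model the 24-month effect is a simple combination of terms.

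**Conclusion.** The point holds and should be fixed. The model sentence is not estimable as literally written. Under the best-supported reading, the conditional baseline adjustment leaves the treatment estimate unchanged. The stated 80% power is not shown to apply to the outcome as named.

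The loss of efficiency is modest: about 9 percentage points of power at ρ = 0.3 (88% against 97%) and 3 at ρ = 0.5 (96% against 99%), with no shortfall below 80% over the range tabulated. This rests on 87 per arm after 30% loss, d = 0.566 inferred from the planned 50, an assumed ρ and no clustering. The consequence of the score ambiguity cannot be sized from the article, but it reaches both the primary test and the stopping decision.

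**What to change.** Replace the sentence with one estimable model of the follow-up scores: arm, categorical time, arm-by-time and a random intercept, with the baseline score always included rather than made conditional on observed imbalance. State that the primary test is the 24-month arm difference from that model, and use the matching 12-month contrast for the DSMB analysis.

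Name one SVAWS score for the primary outcome, the power statement and the DSMB rule, and make the other scores secondary. The choice is the sponsor's. If the 80% power claim is to stand, the score is the physical violence subscale; if the total score is meant, the power needs restating for it.

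This is a change of wording with no new data or participants. It should be made before the 12-month DSMB analysis and before any unmasking.

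### The baseline score enters the outcome models only if the arms look meaningfully different at baseline; it should always be included, for precision and for a fixed primary model

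*Protocol article*

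**What the plan says.** Under Data analysis, the article specifies mixed-effects models that "incorporate a random intercept term to account for within-subject correlation on repeated measures". On what is modelled it says: "The outcome scores at the three follow-up times will be modeled separately using treatment arm", followed by the "baseline symptom score (if there is a meaningful difference between the study arms at baseline"), time, and an arm-by-time interaction. The sentence covers each model, and so covers the SVAWS: "The primary outcome in the study is violence as measured by the SVAWS" (Assessment of outcomes and follow-up). No other section makes baseline adjustment unconditional, and none says what counts as meaningful.

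Three other places bear on the point:

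- Randomization and blinding stratifies by compound only, so baseline SVAWS is not balanced by design.
- The sample size is for "a minimum of 50 families in each study arm to detect this difference in change in means".
- Data and safety monitoring words the 12-month stopping comparison in terms of change in SVAWS by arm.

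**The concern.** In a randomised trial the case for adjusting for baseline rests on its correlation with the outcome, whether or not the arms happen to differ. A rule triggered by observed imbalance leaves the covariate out of most trials. Three things follow.

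- **Precision is lost.** The outcome vector holds only the three follow-up scores. The random intercept links those scores to one another and does not recover the baseline information.
- **Imbalance below the trigger stays in the estimate.**
- **The primary model is not fixed in advance.** It is settled by a judgement on baseline data, and that judgement could differ from one outcome to the next.

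There is also a mismatch. The sample size and the DSMB rule speak of change, while the final model, without its baseline term, compares follow-up levels.

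**Working it through.** **Inputs from the article**

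- "For 80% power at an *α* level of 0.05"; sidedness is not stated, and two-sided is assumed here.
- Target: "a 20% reduction in SVAWS physical violence subscale score among intervention participants at a 24-month follow-up", sized "using a two-sample independent means *t* test", giving 50 per arm.
- Final sample 248 families allocated 1:1, about 124 per arm; up to 30% loss leaves 0.7 × 124 ≈ 87 per arm (Modification to study protocol after initiation of the trial).
- Baseline SVAWS physical subscale 60.7 (SD 16.8), n = 248 (Table 3).

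**Assumptions**

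- ρ, the correlation between baseline and follow-up score, is not given; 0.3, 0.5 and 0.6 are used.
- Equal SDs, normal approximation, one follow-up contrast.
- For step 4, the trigger is taken as baseline p < 0.05, since the article gives none.

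**1. The plan's own figure.** The planning mean and SD are not given, so the 50 per arm cannot be rebuilt from its inputs. It implies d = (1.960 + 0.842) × √(2/50) ≈ 0.56. From Table 3, a 20% reduction is 0.20 × 60.7 = 12.14 points, and 12.14/16.8 = 0.72. Nothing here shows that 50 is wrong.

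**2. Precision.** Adjustment multiplies the variance of the contrast by 1 − ρ². Omitting the covariate therefore inflates it by 1/(1 − ρ²):

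| ρ | 1 − ρ² | 1/(1 − ρ²) | equivalent of 50 per arm |
|---|---|---|---|
| 0.3 | 0.91 | 1.10 | 46 |
| 0.5 | 0.75 | 1.33 | 38 |
| 0.6 | 0.64 | 1.56 | 32 |

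**3. Power.** Power = Φ(d / [√(2/n) × √(1 − ρ²)] − 1.96), with ρ = 0 for the unadjusted test. At n = 87, √(2/87) = 0.152.

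| d | n per arm | unadjusted | ρ = 0.3 | ρ = 0.5 | ρ = 0.6 |
|---|---|---|---|---|---|
| 0.56 | 87 | 95.9% | 97.2% | 98.9% | 99.6% |
| 0.35 | 87 | 63.6% | 67.7% | 76.0% | 82.3% |
| 0.56 | 124 | 99.3% | 99.6% | 99.9% | >99.9% |

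The conditional rule stays close to the unadjusted column. In a simulation at 124 per arm with an effect giving about 80% unadjusted power, a p < 0.05 trigger adjusted in about 5% of trials. Power was then 80% and 81% at ρ = 0.3 and 0.5, against 83% and 90% when always adjusting.

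**4. Type I error.** For an observed baseline difference of k standard errors, the unadjusted test rejects under the null with probability 1 − Φ((1.96 − ρk)/√(1 − ρ²)) + Φ((−1.96 − ρk)/√(1 − ρ²)).

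| | ρ = 0.3 | ρ = 0.5 | ρ = 0.6 |
|---|---|---|---|
| k = 0 | 4.0% | 2.4% | 1.4% |
| k = 1 | 5.0% | 4.8% | 4.5% |
| k = 1.5 | 6.2% | 8.2% | 9.3% |
| k at which it passes 5% | 1.01 | 1.03 | 1.07 |
| average over all k below 1.96 | 4.7% | 4.3% | 4.0% |

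About 69–71% of trials fall below the crossing point. About 27% fall between 1 and 1.96 SE.

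**5. Bias from an imbalance left in.** The SE of the baseline difference is 16.8 × √(2/124) = 2.13 points. At 1.5 SE (3.2 points) the unadjusted estimate shifts by ρ × 3.2: 1.0, 1.6 and 1.9 points at ρ = 0.3, 0.5 and 0.6. The target difference is 12.14 points on the Table 3 mean.

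**The case against.** The strongest reply is that this is a matter of efficiency. At the effect implied by the plan's own sample size, unadjusted power at 87 per arm is already about 96%, so always adjusting adds only 1 to 4 points, and under 1 point at 124 per arm. The correlation is unknown, and the entry cut of 38 on the SVAWS together with a 24-month gap could lower it. All of this stands, and it limits the severity.

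A reader might infer that the rule inflates the false-positive rate. It does not. Averaged over chance imbalance the error is slightly conservative, and it passes 5% only when the baseline difference exceeds about 1 SE. Nor can a large imbalance simply be assumed to stay below the trigger. A 0.25 SD difference on the 124 per arm with baseline data gives z = 0.25/√(2/124) = 1.97, p = 0.049, so a p < 0.05 rule would already adjust for it.

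A reader might also infer that the model can be chosen on trial results. The condition uses baseline data only, recruitment and randomization were complete by December 2016, and the analysts are masked. That limits steering, though it does not make the model prespecified.

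It can be said too that a threshold for meaningful belongs in an analysis plan that is not shown. That is fair for the missing threshold alone. The point here is the stated rule, which would remain the inferior choice with any threshold supplied.

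Finally, the article does not say that the condition applies to the DSMB comparison, which is worded as change and so already uses baseline in some form. What remains there is that the interim and final analyses may estimate different contrasts.

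**Conclusion.** The point holds as one of efficiency and prespecification, and should be fixed. Making adjustment conditional on an undefined baseline difference gives up a variance reduction of 9% to 36% for ρ of 0.3 to 0.6, leaves smaller chance imbalances uncorrected, and leaves the primary model open until baseline data have been judged. The loss in power is small at the planned effect. It is material for a smaller one: 4 to 19 percentage points at d = 0.35 with 87 per arm. These sizes rest on the assumed ρ, on 30% loss, and on a simple two-arm contrast at one time point. The d of 0.35 is illustrative and is not in the article. The documents do not support calling this a validity failure.

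**What to change.** Delete the bracketed condition. State that the baseline value of the outcome is a covariate in every continuous-outcome model, whatever the observed difference between arms. Use the same baseline-adjusted model for the 12-month DSMB comparison, so that the stopping decision and the final analysis estimate the same contrast.

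The cost is one sentence in the analysis section and a matching phrase in the monitoring section. No new data are needed: the SVAWS was part of the eligibility screener, so every enrolled woman has a baseline value for the primary outcome.

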### Modification to study protocol after initiation of the trial

We modified the delivery of CETA from group to individual. After the first few weeks of intervention delivery, multiple participants were missing group sessions due to logistical challenges (e.g. work, funerals), which necessitated CETA providers to conduct separate individual sessions for participants that were absent. It became challenging for providers to keep up with the many in-between group sessions they had to conduct, and then also had to repeat material in groups if an individual missed and was not available in-between group sessions. Participants also indicated frustration in that they did want to participate but there was no flexibility for tardiness (in Zambia, this may be defined as an hour or more late) or work/family scheduling within groups. The challenges were substantial enough that we would not recommend group CETA in Lusaka, Zambia (urban area), even if it was found to be clinically effective. We therefore modified CETA to be individually delivered. Participants initiating CETA before this change could switch to receiving individually delivered CETA or continue to attend group sessions based on their preference and the counselor's assessment of feasibility.

We increased our sample size because of this modification to the delivery of CETA. We plan to conduct a subgroup analysis of only those study participants who received individual (and not group) CETA to test whether this individual delivery mode is effective compared with the TAU control group. Of the 83 families originally randomized to CETA, 33 men and 40 women did not receive a group session (only individual session or sessions). Our original sample size calculation for the CETA arm was *n* = 50. To have at least *n* = 50 CETA participants who received individually delivered therapy, and taking into account potential for up to 30% loss to follow-up, we recruited and randomized an additional 80 families (again randomizing using 1:1 allocation). The final sample size for the study is thus *n* = 248. All the families recruited in this second cohort that were randomized to the CETA arm are receiving individually delivered CETA.

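### The planned test of individually delivered CETA selects the CETA side by treatment received after randomisation, although the second cohort offers a randomised comparison of the same question

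*Protocol article*

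**What the plan says.** All statements below except the last come from the article's section on modifications after initiation of the trial.

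- **The analysis.** After delivery moved from group to individual sessions, the authors plan a "subgroup analysis of only those study participants who received individual (and not group) CETA to test whether this individual delivery mode is effective". The comparator is the TAU arm, with no restriction by cohort stated.
- **How first-cohort participants came to have individual sessions.** Missed groups "necessitated CETA providers to conduct separate individual sessions for participants that were absent". People who had begun before the change "could switch to receiving individually delivered CETA or continue to attend group sessions based on their preference"; feasibility, as judged by the counselor, also counted.
- **The count.** "Of the 83 families originally randomized to CETA, 33 men and 40 women did not receive a group session (only individual session or sessions").
- **The enlargement.** To reach at least 50 individually treated CETA participants, and "taking into account potential for up to 30% loss to follow-up, we recruited and randomized an additional 80 families". Allocation was 1:1 as before, and the total became 248.
- **The second cohort.** "All the families recruited in this second cohort that were randomized to the CETA arm are receiving individually delivered CETA".
- **The primary analyses.** The Data analysis section makes these intent-to-treat, with all randomised participants included. That commitment is worded for primary analyses and does not reach this subgroup test.

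**The concern.** Randomisation protects a comparison only if both sides are kept as randomised. Here the CETA side is cut down by something that happened afterwards (no group session, at least one individual session), and the TAU side is not cut down at all. In the first cohort the routes into the individual-only group are non-randomised: missing the groups, starting CETA later, or something else the article does not describe. Any of these could be related to later violence or drinking. CETA participants who attended nothing also fall out, while their TAU counterparts stay in.

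The test carries weight. The authors say they would not recommend group delivery in this urban setting even if it proved clinically effective, so the individual-delivery result is the one that will inform practice. It was also the reason for recruiting 80 more families. Yet the article already contains a randomised comparison of individual CETA with TAU, in the second cohort, and does not use it for this purpose.

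**Working it through.** **Inputs from the article.** 83 first-cohort CETA families; 33 men and 40 women with individual sessions only; 80 further families, 1:1; 248 in total; 30% loss; 50 per arm for 80% power at alpha 0.05; a 20% reduction in the SVAWS physical violence score; baseline mean 60.7, SD 16.8. **Assumed:** exactly 40 per arm in the second cohort, and a two-sided test.

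**1. Reproducing the 80 families.** 50 / 0.7 = 71.4, so 72 individually treated CETA participants are needed. Men: 72 − 33 = 39 more; doubled for 1:1, 78 families, close to the stated 80. Women: 72 − 40 = 32 more, or 64 families, so the figure rests on the men's count. Check: (33 + 40) × 0.7 = 51.1 men and (40 + 40) × 0.7 = 56 women, both at least 50. The figure works only if first-cohort participants are counted by treatment received, which confirms that the two cohorts are pooled in this test.

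**2. Cohort mix.** First cohort: 248 − 80 = 168 families, so TAU = 168 − 83 = 85. Total TAU = 85 + 40 = 125.
- First-cohort share of individual-CETA women: 40/80 = 50%; men: 33/73 = 45%.
- First-cohort share of TAU: 85/125 = 68%.

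**3. Family unit.** Families were randomised together. With 40 women but 33 men individual-only, at least 40 − 33 = 7 of those women had a partner who was not in the same category.

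**4. Possible bias (women, who report the primary outcome).** Let D be the prognostic difference of individual-only women, in SD units. The article gives no value.
- If D is measured against the first-cohort average, the shift is 0.50 × D.
- If D is measured against the other 43 first-cohort CETA women, it is 0.50 × (43/83) × D = 0.26 × D.

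| Assumed D | Shift in the individual-CETA mean |
|---|---|
| 0.1 SD | 0.03 to 0.05 SD |
| 0.3 SD | 0.08 to 0.15 SD |
| 0.5 SD | 0.13 to 0.25 SD |

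The sign of D is unknown.

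**5. Precision of the randomised alternative.** The second cohort has 40 v 40, or 40 × 0.7 = 28 v 28 after 30% loss. Two planning effects are considered:
- d = 0.57 (0.566), the effect for which 50 per arm gives 80% power with a t test;
- d = 0.72, from 0.20 × 60.7 = 12.14 and 12.14 / 16.8, taking the baseline SD as the outcome SD.

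| Comparison | Power at d = 0.57 | Power at d = 0.72 |
|---|---|---|
| Second cohort, 40 v 40 | 71% | 89% |
| Second cohort, 28 v 28 | 55% | 76% |
| Pooled as received, about 51 to 56 v 87 | 89 to 91% (nominal) | 98 to 99% (nominal) |

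The last row is power for a comparison that is not fully randomised. Approximate 95% half-widths are 1.96 × √(2/28) = 0.52 SD for the second cohort and 1.96 × √(1/56 + 1/87) = 0.34 SD for the pooled comparison in women. To keep 50 per arm after 30% loss, the second cohort alone would have needed 2 × 72 = 144 families.

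**The case against.** The strongest reply is that this is a labelled subgroup analysis. The primary analyses are intent-to-treat and the 12-month stopping rule compares the randomised arms, so the trial's main claim is untouched. That stands, and it limits the severity.

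Three further limits also stand.

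- **Self-selection.** A reader might infer that the 40 women and 33 men chose their delivery mode. The article does not support this. The preference and feasibility clause applies to those who started before the change, and anyone who attended a group and then switched is outside the individual-only count. Some of those counted may simply have started later, and missed groups are put down to work, funerals and similar logistics. What can be said is that the status was fixed after randomisation and not by it.
- **An uninterpretable result.** A reader might conclude that nothing from the pooled test can be attributed to individual CETA. That goes too far: 40 of the 80 women and 40 of the 73 men on the CETA side come from an arm randomised to individual delivery. The result is open to bias but still carries information.
- **Cohort mix.** The whole TAU arm is the natural reading of the comparator, but the article does not name cohorts, and nothing in it shows that the cohorts differ in prognosis.

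It can also be said that model terms belong in an analysis plan that is not shown. That does not answer the point, because the article itself fixes the population by treatment received and sizes the enlargement on it.

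**Conclusion.** The point holds for this subgroup test and for the enlargement built on it. The test mixes a randomised component (second cohort) with one selected after randomisation (first cohort) and compares the mixture with an unselected TAU group. Neither the direction nor the size of the resulting bias can be derived from the article. The illustrative 0.08 to 0.15 SD rests wholly on the assumed 0.3 SD difference, and is about 14% to 27% of d = 0.566. The cohort-mix figures assume the whole TAU arm as comparator and an even split of the second cohort.

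A reader might take this as a threat to the main CETA v TAU result; it is not one. It should be fixed, because the subgroup result is the one that speaks to the delivery mode the authors intend to recommend, and a randomised answer is available in the same data.

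**What to change.** 1. Rest any claim about individually delivered CETA on the second cohort as randomised: all families assigned CETA against all assigned TAU, including CETA families who attended no session. Estimate it as the cohort-specific effect from an arm-by-cohort term in the intent-to-treat model, crossed with time where the model carries a treatment-by-time interaction.
2. Keep the pooled as-received comparison as supportive. Label it non-randomised, adjust it for cohort and baseline SVAWS, and state which TAU families it uses.
3. State the limited precision with both planning effects, since a single power range would present one assumption as fact: about 28 v 28 after 30% loss, below the protocol's own 50 per arm, with power of 55% (71% with no loss) at d = 0.57 and 76% (89%) at d = 0.72.

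The cost is wording and one model term, with no new participants. The real price is a wider interval for the individual-delivery effect, about ±0.52 SD in place of ±0.34 SD. The change should be made before outcome data are unmasked.
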